## **Language**

All materials will be available in English and French.

## **Protecting against sources of bias**

### *Contamination between intervention and control:*

This will be a controlled before and after study, with simultaneous crossover of all study units into the intervention period. Allocation of the intervention in a before and after fashion will avoid contamination between units, as medical staff might be enticed to increase deprescription for all admitted gabapentinoid users once the educational brochures are handed out, regardless of the intervention group of the participants. **Inter-site** contamination between intervention and control groups is limited by the simultaneous crossover of all sites. Indeed, it is common for medical staff and residents to rotate at all study sites during a given year. If we were to have different units simultaneously in the control and intervention periods, we could expect a source of contamination by having medical staff rotate from an intervention site to a control site afterwards.

At each hospital, it is possible that a participant will be admitted prior to the transition from control to intervention. Participants enrolled during the control period who remain inpatients when the site is switched over to the intervention period will remain in the control arm.

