## Research design and methodology

This will be a prospective controlled before and after study involving two centres: the McGill University Health Centre (MUHC) Glen Site (Royal Victoria Hospital) and the Montreal General Hospital. The control and intervention units will be the five medical units.

The study will begin in the control period. Based on previous study data regarding the prevalence of admitted gabapentinoid users and the average number of monthly admissions on the clinical teaching units, recruitment in the control period should last approximately 12 months. All study sites will simultaneously transition to the intervention period after 80 patients have been recruited (estimated 1 year). The rationale for simultaneous transition of all units is to reduce the risk of inter-site contamination of the intervention, as it is common for medical residents and staff to work in all the study sites during a given year. The decision to transition to the intervention period after 80 patients have been recruited is motivated by the need to reduce the risk of bias introduced by temporal trends in deprescribing secondary to level of training of junior residents and seasonal variations of workload on the medical wards. If the target number of control participants is reached before the 12-month mark, recruitment will be suspended until then. The intervention period will be completed once the pre-specified target number of 80 intervention participants is reached, which is expected to take approximately 12 months as well.

Follow up of discharged patients will be at 8 weeks post-discharge. We will analyze and publish the results afterwards.

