#### ***1. In-hospital patient educational brochure:***

Participant's medication list will be identified from the pharmacy database and validated with the participant's best possible medication history taken at time of admission by the pharmacist. Eligibility will be confirmed by the participant's treating medical team with support from the study investigators. Participants who are enrolled during the intervention phase will receive an educational brochure (see appendix) about the risks of chronic gabapentinoid use and how to stop using them. The rationale for the structure of the brochure has been presented in detail [24] and it has been validated in both English and French for comprehension and readability, including for people with mild cognitive impairment [27].

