#### ***2. Educational session toward physicians about gabapentinoid prescriptions:***

An educational session about the purpose of the study and risks of gabapentinoid prescriptions will be delivered to physicians (staff and medical residents) on each unit at both sites during the intervention period. The educational session will include a presentation by a member of the team at the monthly teaching rounds and an electronic message sent to all physicians on the medical service. They will also be presented a brief overview of the educational brochures.

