## **Justification of sample size**

The estimated sample size is 160 participants, with 80 in the control group and 80 in the intervention group. The sample size was calculated to detect an absolute increase of 20% in deprescription rates with the intervention (number needed to treat 5), allowing for a two-sided type 1 error of 5% and a type 2 error of 20%. Based on the results of a previous retrospective descriptive study of gabapentinoid prescriptions in medical inpatients, the control period event rate (discontinuation) is expected to be 13% [8]. The expected loss to follow-up is approximately 15%, including deaths.

There are approximately 50 patients admitted per month on each clinical teaching unit (total 200 admissions across the study units), of which 13% are expected to be taking gabapentinoids prior to admission [8]. Approximately 75% of admitted gabapentinoid users are aged 60 years and older. Assuming a refusal rate of 15%, as seen in the EMPOWER study [26], we expect a maximum of 16 participants enrolled per month.

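### If control accrual takes the expected 12 months or longer, nothing separates the last control enrolment from the switch, so a few controls still in hospital will meet the physician part of the intervention

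*Protocol*

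**What the plan says.** The Protocol's section on research design and methodology ties the switch to recruitment: "All study sites will simultaneously transition to the intervention period after 80 patients have been recruited (estimated 1 year". It adds one conditional pause: "If the target number of control participants is reached before the 12-month mark, recruitment will be suspended until then".

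The section on contamination between intervention and control foresees patients who are caught by the switch. Control participants "who remain inpatients when the site is switched over to the intervention period will remain in the control arm". Nothing further is said about them.

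The intervention has two parts. The brochure is limited by period of enrolment: "Participants who are enrolled during the intervention phase will receive an educational brochure". The physician session is not limited to particular patients. It "will be delivered to physicians (staff and medical residents) on each unit at both sites during the intervention period", and consists of "a presentation by a member of the team at the monthly teaching rounds and an electronic message sent to all physicians on the medical service".

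The statistical analysis plan section of the Protocol analyses participants by period under intention to treat. The one sensitivity analysis it names for the primary outcome concerns deaths and losses to follow-up.

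**The concern.** The section on controls defines the control condition as usual care from staff who have had no specific information about the trial and no deprescribing instructions. A control who is still on the ward after the switch no longer receives that condition once the physicians there have been taught or messaged.

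The Protocol accepts the mechanism itself. In arguing against concurrent arms, the contamination section says that "medical staff might be enticed to increase deprescription for all admitted gabapentinoid users once the educational brochures are handed out", whatever group the patient is in. The argument is applied to contamination between units and sites. It is not applied to patients who straddle the switch, who are dealt with in the next paragraph.

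The exposure falls at a sensitive time. By the Protocol's own background, the 13% historical rate counts cessation, or a taper with intent to stop, at discharge, and deprescribing started in hospital succeeded more often than deprescribing started afterwards. A straddler's discharge prescription is written after the switch.

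At stake is a control rate that is somewhat too high, and so an effect estimate that is somewhat too small, in a trial whose power has no reserve after the expected losses.

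**Working it through.** **Inputs from the Protocol (justification of sample size; research design).** Control rate 13%; absolute increase 20 points, so 33% under the intervention; two-sided 5%; power 80%; loss 15%; 80 per group; about 12 months for the control period; at most 16 enrolled a month.

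**Assumed.** Length of stay is not given. I take 7, 14 and 28 days.

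**1. The plan's own figure.** For two proportions (normal approximation, pooled variance under the null, no continuity correction):

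n = [1.96 × √(2 × 0.23 × 0.77) + 0.8416 × √(0.13 × 0.87 + 0.33 × 0.67)]² / 0.20² = 68.3, so 69 per group.

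For 15% loss, 69 × 1.15 = 79.4, so 80; dividing instead, 69 / 0.85 = 81.2, so 82. The stated 80 is reproduced. With 80 × 0.85 = 68 evaluable per group, power is 79.8%.

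**2. Is there a gap before the switch?**
- 80 controls in 12 months or longer: the suspension rule does not operate, and the gap is zero.
- 80 controls at 16 a month: 80 / 16 = 5 months, then suspension to month 12, a gap of about 7 months. Almost no control would still be in hospital.

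**3. Controls in hospital at the switch, with no gap.** Expected number = monthly accrual × stay / 30.4, with accrual 80 / 12 = 6.67. Highest control rate = 13% + 20 points × share, as if each straddler received the full effect.

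| Assumed stay | Straddlers | Share of 80 | Highest control rate | Difference left |
|---|---|---|---|---|
| 7 days | 6.67 × 7 / 30.4 = 1.5 | 1.9% | 13.4% | 19.6 points |
| 14 days | 6.67 × 14 / 30.4 = 3.1 | 3.8% | 13.8% | 19.2 points |
| 28 days | 6.67 × 28 / 30.4 = 6.1 | 7.7% | 14.5% | 18.5 points |

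**4. Power.** With 85% of straddlers evaluable, 1.5, 3.1 and 6.1 become 1.3, 2.6 and 5.2, or about 1, 3 and 5 of 68.

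| Evaluable straddlers | Power, full effect | Power, half effect |
|---|---|---|
| 0 | 79.8% | 79.8% |
| 1 | 78.4% | 79.1% |
| 3 | 75.5% | 77.7% |
| 5 | 72.4% | 76.2% |

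The full-effect figures are upper bounds on the harm, for three reasons. Straddlers receive no brochure. Only the time from enrolment to discharge counts, and it is shorter than the whole stay. The teaching is given at monthly rounds, so some straddlers may leave before a session takes place.

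**The case against.** The strongest reply is that the plan already limits the problem. Only controls in hospital on the day of the switch are affected, the brochure is withheld from them, and early completion of accrual triggers a pause. Keeping them as controls is stated openly and agrees with analysis by period under intention to treat; moving or dropping them by outcome or by length of stay would be worse. The error is towards no difference, so it cannot produce a false positive result. All of this stands. It limits the size of the point but does not remove it: on the timeline that the Protocol expects, the pause does not operate.

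A reader might infer more than the document supports:
- **That the control arm as a whole is contaminated, or that contamination is certain.** Exposure depends on accrual speed, length of stay and teaching dates, and concerns a handful of patients.
- **That faster accrual makes matters worse.** At 16 a month the formula in step 3 gives about 4, 7 or 15 straddlers. But at that rate recruitment stops at month 5 and the switch waits until month 12, so these numbers cannot arise.
- **That controls discharged shortly before the switch are exposed as well.** With a 14-day stay, 6.67 × (56 + 14) / 30.4 = 15.4 controls (19% of 80) have some of the time to their 8-week assessment after the switch. They would be exposed only if readmitted to a study unit, and the Protocol gives no readmission rate. The 19% is an opportunity for exposure, not a contamination rate.
- **That the physician session carries half of the effect.** The Protocol presents the brochure as the tool under evaluation and the sessions as a supplement, and gives no split.

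**Conclusion.** The point holds in a limited form. If control accrual takes 12 months or longer, the Protocol leaves no interval between the last control enrolment and the switch, and some controls will be discharged by physicians who have had the education and the message.

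On assumed stays of 7 to 28 days, this concerns about 1.5 to 6 of 80 controls. It raises the control rate from 13% to at most about 13.4–14.5% and takes at most about 0.4 to 1.5 points off the 20-point difference. The direction, towards no difference, assumes only that teaching physicians does not reduce deprescribing. If 80 is reached well before month 12, the problem all but disappears.

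The fault lies in the avoidable exposure, not in the decision to keep these patients as controls. The effect is modest, but power is already 79.8% at the expected loss and the remedy is cheap, so the change is worth making.

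**What to change.** 1. **Make the pause unconditional.** In the sections on research design and on contamination, set a short fixed interval between the last control enrolment and the first physician session, electronic message and brochure. About 4 weeks is an example; it should be set from the units' usual length of stay. The switch then falls at month 12 or at the end of this interval, whichever is later. A fixed interval is better than waiting for the last control to be discharged, which would tie all five units to one long-stay patient.
2. **Keep any remaining straddlers as controls** under intention to treat, and record and report how many there are.
3. **Add a sensitivity analysis of the primary outcome** that omits all controls enrolled within a fixed window before the switch. The window must be longer than the pause, or it removes nobody. For example, 8 weeks with a 4-week pause omits about 6.67 × 28 / 30.4 = 6 controls. The rule should go by enrolment date, not by length of stay or readmission: selecting on those would remove sicker controls with no counterpart in the intervention group.

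**Cost.** Protocol wording, no added patients, and a delay of a few weeks. The delay fits within the stated 24–36 months, although the planned end in April 2023 would move by about as much. The two periods would align slightly less well by season and academic year, which the Protocol wants to match; a short pause keeps that shift small.

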### *Blinding:*

It will not be possible to blind participants or physicians in this study. However, this is typical in pragmatic study designs, and we do not expect that this will have a substantial impact on our results. Blinding the assessment of outcome will be critical to ensure valid study results and we have tried to select as many hard outcomes as possible, including validated standardized questionnaires, that do not involve individual judgement by the assessor.

In the control period of this study, participants will be informed that the study will be evaluating medications and post-discharge changes but will not be aware that gabapentinoids will be specifically studied, in order to reduce selection bias. Accordingly, medical staff will not be aware of the specifics of the study during the control period.

### *Other:*

Given the simultaneous crossover of all sites into the intervention period, our study might be subject to temporal trends in deprescription of gabapentinoids over the year, which could be influenced by

factors such as training level of junior residents or time-constraints from seasonal variations of workload intensity on the clinical teaching unit. However, previous retrospective data has not shown any temporal trends for gabapentinoid deprescribing on medical wards [8]. The control period and intervention periods will be spaced out such that they will bridge the academic year as best as possible.

### **Quality Control / Quality Assurance**

Ongoing quality control and quality assurance will be reviewed in regular research team meetings throughout this study to identify any concerns about the implementation of the intervention, data collection and/or analysis.

### **Ethical considerations, consent, privacy and confidentiality**

The study will be conducted in compliance with TCPS 2 (2018), as well as in respect of the requirements set out in the applicable standard operation procedures of the Research Institute of the McGill University Health Centre and of the McGill University Health Centre Research Ethics Board. Ethics approval will be obtained through the McGill University Health Centre Research Ethics Board.

Participant information will be compiled using the MUHC Research Institute REDCap software. Data will be coded with the use of a unique code for each participant. Access to the database will be limited to the study investigators and research assistants and will require a two-factor authentication. Only study investigators will have access to the final study data.

Some subjects may only agree to participate in the study if they are exempt from the follow up phone calls. Such patients will still be enrolled if they consent to our use of the DSQ to evaluate the primary endpoint but will be excluded from some of the secondary analyses.

Patients who are cognitively impaired or otherwise unable to provide consent will not be included. Although this subpopulation of patients may still greatly benefit from deprescription of potentially inappropriate medications, the educational brochures used in this study rely on instigating motivation and providing self-capacity, and are therefore intended for patients who are cognitively intact or have only a mild form of cognitive impairment [27]. Although distribution of the educational brochures to the patient's proxy could be considered, this strategy is less feasible in the context of the SARS-CoV-2 pandemic, as family and caregivers have limited access to the bedside, hindering contact with medical staff, which is crucial for initiation of the deprescription process.

Patients who are ultimately transferred to and discharged from non-study units during their hospitalization will be excluded unless that unit is a transitional care, rehabilitation, or post-acute care unit used only to bridge the gap between acute medical hospitalization and community services.

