## **Data collection**

Information about participants will be collected by the research assistants from the participants and their medical record. We will abstract reason for admission, comorbidities and other medications from the chart. At time of enrollment, we will obtain consent to directly obtain prescription history from the *Dossier Santé Québec* (DSQ), which is a prescription record database for all patients in Québec, as well as from the community pharmacy from which participants receive their medications. These will serve to validate deprescription. During the index admission, a first questionnaire will be administered in person and will collect information about demographics, including age, gender and residence style (independent, assisted living, etc.). We will also obtain a medication use history (for study drugs) and standardized questionnaires to assess global functioning, pain control and cognition. Follow up questionnaires will be administered at 8 weeks after hospital discharge by telephone. The follow-up questionnaire will collect any demographic changes such as destination of discharge and length of stay, will ask participants about deprescription (cessation, reduced use, intent to reduce, or no change), initiation or dose increase of other pain medications, occurrence of withdrawal symptoms, and finally will repeat the global functioning, pain control and cognition questionnaires.

Death will be determined from hospital records. Participants who are known to have died before 8 weeks post-discharge will be excluded from the analysis of the primary outcome (as they cannot attain it); however, they will be retained in the study for descriptive purposes and other outcomes.

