### Statistical analysis plan

We will use an "intention to treat" principle. We will analyze participant data according to their participation during the intervention or control period. For the primary outcome, we will perform a sensitivity analysis for patients who died or were lost to follow-up using the most recent available data on their gabapentinoid use (inpatient pharmacy records, discharge prescriptions or the provincial electronic medical record). We will assess binary outcomes using binomial regression comparing the intervention to no intervention and adjusting for age and sex. We will assess continuous outcomes (T scores) using linear regression comparing the intervention to no intervention, adjusting for baseline values, age and sex.

We will perform several preplanned subgroup analyses for the primary outcome, including an analysis of participants aged 80 or older; analyses based on reason for admission, discharge destination (community v. long-term care facility) and comorbidities; and an analysis looking at the effect of each study unit. Subgroup analyses will be treated as hypothesis generating and presented graphically with 95% confidence intervals.

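### Enrolled patients discharged from a non-study unit are excluded, which contradicts the intention-to-treat analysis by period and is covered by no sensitivity analysis

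*Protocol*

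**What the plan says.** - **Analysis principle.** The Statistical analysis plan section of the Protocol adopts intention to treat and adds: "We will analyze participant data according to their participation during the intervention or control period".
- **Transfers.** The section on ethical considerations, consent, privacy and confidentiality says: "Patients who are ultimately transferred to and discharged from non-study units during their hospitalization will be excluded". The sentence goes on to exempt transitional, rehabilitation and post-acute units that bridge to community services. The list under Inclusion and exclusion criteria has no such rule.
- **Deaths.** Under Data collection, patients known to have died before 8 weeks "will be excluded from the analysis of the primary outcome (as they cannot attain it"). They are kept for description and for other outcomes.
- **Sensitivity analysis.** For the primary outcome, "we will perform a sensitivity analysis for patients who died or were lost to follow-up using the most recent available data". Transferred patients are not mentioned.
- **Outcome source.** Opting out of the DSQ is an exclusion criterion, and consent to DSQ and community pharmacy records is taken at enrolment. For patients who decline the follow-up calls: "Such patients will still be enrolled if they consent to our use of the DSQ to evaluate the primary endpoint".
- **Sample size.** 80 per group, 13% versus 33%, two-sided 5% error, 80% power, and about 15% loss to follow-up with deaths included.

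**The concern.** A patient consents, completes the baseline questionnaire and, in the intervention period, receives the brochure, all during the admission. Whether that patient later leaves from a study unit is decided afterwards. Removing the patient on that basis conditions the primary analysis on an event after exposure, which intention to treat is meant to prevent.

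There is no randomisation here to balance who is transferred. The two groups are recruited about a year apart, and the Protocol itself names seasonal workload and residents' level of training as possible influences over time. If the share or the kind of patients transferred differs between the periods, the comparison of deprescription rates shifts for reasons unrelated to the brochure. No planned analysis would reveal this, because the sensitivity analysis brings back only deaths and losses to follow-up.

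The exclusion is also avoidable. A living transferred patient still has a DSQ or pharmacy record at 8 weeks.

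**Working it through.** **1. The Protocol's own sample size.** Inputs from Justification of sample size: p1 = 0.13, p2 = 0.33, d = 0.20, mean p = 0.23.

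n = [1.960 × √(2 × 0.23 × 0.77) + 0.842 × √(0.13 × 0.87 + 0.33 × 0.67)]² / 0.20²
= [1.960 × 0.5952 + 0.842 × 0.5781]² / 0.04 = 68.3, so 69 per group.

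Allowing for 15% loss, 69 / 0.85 = 82, or 69 × 1.15 = 80. The stated 80 per group is reproduced within two patients.

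**2. Power at the number analysed.** Power = Φ[(0.20 × √n − 1.960 × 0.5952) / 0.5781].

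| Situation | n per group | Power |
|---|---|---|
| All 80 analysed | 80 | 85.9% |
| Planned 15% loss (80 × 0.85) | 68 | 79.8% |
| 15% loss plus 5% transfers (80 × 0.80) | 64 | 77.3% |
| 15% loss plus 10% transfers (80 × 0.75) | 60 | 74.6% |
| 15% loss plus 15% transfers (80 × 0.70) | 56 | 71.6% |

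The transfer percentages are assumptions; the documents give none.

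**3. Bias illustration.** Assume no true effect (13% in both periods), with 5% excluded in the control period and 15% in the intervention period. Let q be the deprescription rate among the excluded.

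Control rate seen = (0.13 − 0.05q) / 0.95. Intervention rate seen = (0.13 − 0.15q) / 0.85.

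| q | Control | Intervention | Spurious difference |
|---|---|---|---|
| 0% | 13.7% | 15.3% | +1.6 points |
| 30% | 12.1% | 10.0% | −2.1 points |
| 50% | 11.1% | 6.5% | −4.6 points |

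The sign depends on q, so the direction cannot be known in advance. If the same share with the same q were excluded in both periods, this spurious difference would be zero.

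**4. Coverage of the rules.**

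| Group | In the exclusion list? | In the primary analysis? | In the sensitivity analysis? |
|---|---|---|---|
| Transferred, discharged from a non-study unit | No | No | No |
| Died before 8 weeks | No (only expected deaths) | No | Yes |
| Declines follow-up calls | No | Yes, through DSQ | Not needed |

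Transferred patients are the only one of these groups that no planned primary-outcome analysis includes.

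**5. Deaths (secondary).** The primary outcome includes a prescribed taper as well as cessation, so a patient could have met its content before dying. "Death will be determined from hospital records", while cessation is confirmed from DSQ or pharmacy records. A death outside hospital that goes unnoticed would show as no further dispensing. One such case counted as cessation adds 1/80 = 1.3 to 1/68 = 1.5 points to its group. The number of such cases is unknown.

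**The case against.** **The excluded group may be small.** The exception keeps common onward routes after acute care, and no transfer rate is given. That stands, and it limits the likely size. It does not remove the contradiction.

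**Transfers may already be inside the 15%.** The allowance names deaths but does not say that nothing else is counted. That also stands, so the loss of power is conditional. If transferred patients were replaced until 80 remained, the extra loss of power would disappear, but the selection would not. The Protocol does not mention replacement.

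**The sample size is wrong.** A reader might infer this from the power table. It is not: the 160 is reproduced.

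**Patients who miss the telephone call are dropped.** A reader might infer this because loss to follow-up is undefined and appears only in the sensitivity analysis. No text says so, and those who decline calls are kept through the DSQ. Lack of phone contact is an eligibility criterion, not a stated ground for removing someone enrolled.

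**The same DSQ data are handled in opposite ways.** This does not follow either. For patients who decline calls, the DSQ evaluates the 8-week endpoint. In the sensitivity analysis, the provincial record is one of several sources for a last available status.

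**Excluding deaths is an outright error.** This goes too far. A patient who died has no 8-week status, the exclusion is stated openly, and a last-record analysis is planned. Which of the two is primary is largely a choice of estimand. What remains is that the reason given fits poorly with an endpoint that a prescribed taper can meet. As for unnoticed deaths, the 8-week call would often reveal them, so that gap lies mainly with patients who are not reached or are exempt from calls.

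**Conclusion.** The contradiction over transfers holds on the Protocol's own text and needs no assumption. Enrolled patients are removed on a later event, the rule is outside the eligibility list, no sensitivity analysis restores them, and the stated principle is intention to treat by period.

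The size is uncertain. Power falls from 79.8% to about 77% to 72% only if transfers come on top of the 15% and amount to an assumed 5% to 15% of those enrolled. The illustrated bias of +1.6 to −4.6 points rests on assumed unequal exclusion (5% versus 15%) and assumed rates among the excluded. No figure in the documents shows that a material bias will occur. The case for acting is that the bias would be undetectable under the present plan and can be avoided at almost no cost.

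The points on deaths are secondary: one is a weak justification with a planned sensitivity analysis behind it, the other a gap in ascertainment of unknown size. The documents do not support a claim that patients lost by telephone are removed.

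**What to change.** 1. Delete the transfer exclusion from the primary analysis and keep it as a sensitivity set. Report the number transferred in each period.
2. State that all enrolled patients are analysed by period, with 8-week status from DSQ or pharmacy records whether or not the patient was reached by telephone. Define loss to follow-up as having no such record.
3. Keep the planned sensitivity analysis for deaths and report it beside the primary result. Reword the reason for excluding deaths so that it agrees with an endpoint that includes a prescribed taper.
4. Before counting absence of dispensing as cessation, require evidence that the patient was alive at 8 weeks: phone contact, or any dispensing dated at or after 8 weeks.

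Cost: wording in three places (Ethical considerations, consent, privacy and confidentiality; Data collection; Statistical analysis plan), settled before the analysis. No new data source is needed. The DSQ may not show an intended taper by itself, so pharmacy contact, already consented to, may be needed for some patients. The deprescription rates may look slightly less favourable.
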